### Participant timeline {13}

The study period for participants in the multicenter cohort study extends from ED admission and study enrollment to the end of the study measures. Primary data collection at t0 is divided into three parts at four time points, including the collection of primary data prior to the use of SmED-Patient (t0-1) and after the use of SmED-Patient (t0-2 and t0-3). The timeline of study measures at baseline (t0) is illustrated in Fig. 1. T0-1 includes patients’ perceived urgency, which is sensitive to the bias of the SmED assessments, and precedes the randomized SmED assessments at t0-2; part 2 at t0-3 includes patients’ utility assessment of SmED-Patient; part 3 at t0-4 includes patients’ reasons for ED presentation and questions on health literacy, characterisation of patients’ complaints, and socio-demographics (see Table 8).

**Fig. 1 Fig1:**
[figure not shown]
Study measures at baseline (t0)

### Sample size {14}

We expect a perfect agreement on the binary care level between SmED-Patient and the expert panel in 70% of the cases. To demonstrate that this agreement exceeds 58.5%, we aim to apply a one-sided binomial test with over 80% power at a significance level of alpha = 0.025. The threshold of 58.5% reflects the minimum level of agreement considered acceptable. Based on this assumption, a sample size of 150 evaluable patients was calculated. Assuming a dropout rate of 25%, a total of up to 200 patients will be enrolled in the multicenter cohort study. The sample size planning was conducted using R version 4.2.1.

The estimate for a perfect agreement on the binary care level is based on the available literature, from which studies using symptom assessment applications and either gold standard vignettes or physician review of cases concur at 62%−63% [29, 30]; reviews and vignette studies found that the triage accuracy of SAAs ranged from 33 to 98%, with the majority of studies relying on vignettes rather than prospective data collection [18, 20, 30]. In this study, we assume 70% agreement and therefore that there will be a higher level of agreement between SmED-Patient and the expert panel than is suggested by the results of previous studies [29, 30]. This is because the assessment of agreement will be limited to the binary care level (i.e., ED or outpatient practice), rather than, for example, four or five triage categories. In case the agreement falls below the expected threshold, qualitative data from providers on the perceived utility of symptom self-assessment can be used to help contextualize the findings. In addition, quantitative data from both providers and patients such as urgency assessments and patient evaluations of SmED-Patient (e.g., ease of use) can support interpretation and provide further insight into potential discrepancies.

For the focus groups, staff from the two participating EDs will be invited to participate in two focus groups (*n* = 2 with each *n* = 5 participants). The focus groups will consist of staff from differently structured EDs to ensure a broad range of perspectives and implementation scenarios in German emergency care: Standard care in the ED, separate low-acuity fast track within the ED (“fast track”). No specific sampling is required for the microsimulation.

### Recruitment {15}

The recruitment follows approaches that have been used in similar studies [21]: Study nurses determine patients’ eligibility for the study through a pre-screening in the ED’s digital documentation system (E.CARE ED). Eligible patients will be approached in the ED waiting area after triage and before the first physician encounter. If eligible patients verbally express interest in participating in the study, study nurses will verbally review inclusion and exclusion criteria and initiate the consent process, including explanation and information about the study, answering questions, and obtaining written consent. Among all ED patients, adult German- and English-speaking patients will be included who present themselves at the ED on a walk-in and self-referral basis and who do not require immediate medical treatment. Patients are eligible if ED staff ask them to wait in the waiting area, indicating no need for immediate ED treatment. No formal triage system is used for the eligibility screening. This approach ensures that a wide range of complaints and urgency levels can be considered.

The prospective patient survey as well as the application of SmED-Patient and SmED-Contact + takes place during the waiting time for the first physician encounter on the day of presentation in the ED. To assist with patient recruitment, student assistants will be involved in the recruitment process. They will receive structured training in patient recruitment and the use of SmED-Contact +. The recruitment period is tentatively planned to be 6 months but will continue until the target number of patients (*n* = 150) is reached.

Recruitment for the focus group interviews will be conducted concurrently with recruitment for the cohort study by distributing flyers and informing ED staff about the study and the focus groups during team time-outs in the ED. Focus group participants will receive a 100 euros voucher for their participation, and an additional 50 euros for evaluating the microsimulation. The microsimulation will be performed by the study team, including students from the Charité-Universitätsmedizin Berlin. Students are recruited through the university’s internal mailing list and are offered a 50 euros voucher for their participation. Experts for the panel will be approached by the study team on the basis of their medical experience in working in the ED or ambulatory setting. Experts receive compensation, including 2,500 euros for written evaluations of 50% of cases and an additional 1,250 euros for case conferences in the event of disagreement. For each of these study measures, interested potential participants will be informed of the study verbally and in writing before written consent is obtained.

## Assignment of interventions: allocation

### Sequence generation {16a}

Patients who participate in the study will be assessed by SmED-Contact + and are asked to conduct a self-assessment using SmED-Patient. In order to control for the potential reciprocal impact on patient responses to the SmED-Patient and SmED-Contact + assessments, the sequence of the two SmED configurations is randomized using RStudio (Version 2024.09.1) and is secured. Block randomization is used for this purpose. The randomization protocol for the multicenter cohort study is implemented in REDCap (block randomization: *n* = 8 per block) and is known to the study coordinator and principal investigator.

The panel of experts will conduct retrospective case reviews of all valid cases.

### Concealment mechanism {16b}

The allocation is unknown to the study staff until the moment the patients confirm their written consent to the study and the study staff starts the digital recruitment documentation in REDCap.

### Implementation {16c}

The study staff initiates the allocation process in REDCap by pressing the randomization button as part of the randomization module in REDCap. The system allocates the patient based on a preloaded block randomization list (*n* = 8 per block), stratified by the two study centers and implemented within REDCap.

## Assignment of intervention: blinding

### Who will be blinded {17a}

The study personnel will be blinded to the SmED-Contact + results to reduce any potential cross-influence on the assessments. To this end, the study will use a version of SmED-Contact + that does not display the assessment recommendation. Patients are blinded to the results of the SmED-Patient recommendation to reduce uncertainty about the recommendation and not to influence patient behaviour. Instead, hypothetical compliance will be asked based on a patient vignette. Study personnel can access recommendation in retrospect through an assessment archive.

The results of the SmED-Contact + and SmED-Patient assessments will be retrieved from a web-based study entity provided by the Zi (see 18a).

### Procedure for unblinding if needed {17b}

Not applicable. Intervention is unblinded and sequence is known after randomization.

## Data collection and management

### Plans for assessment and collection of outcomes {18a}

The project consists of five working modules (see Fig. 2 for an overview).

**Fig. 2 Fig2:**
[figure not shown]
Module overview

#### Module 1: prospective patient survey, retrospective subgroup SmED-Patient symptom overlap and utility assessment, and pilot of nurse assessment of patient urgency and level of care

The first study measures, including the study enrollment, primary data collection, application of SmED-Patient and SmED-Contact +, will be performed in the waiting area of the ED while waiting for ED treatment (see Fig. 1). The primary data collection at baseline is divided into 3 parts, of which part 1 (t0-1) includes an instrument that is sensitive to the influence of the SmED assessments (patient self-assessment of urgency, see Table 4) and part 2 (t0-3) includes instruments that are sensitive to the physician encounter (e.g. reasons for ED presentation, see Table 4). Part 3 is not considered bias-sensitive. It can be collected independently of the time of the physician encounter.

The prospective cohort study will measure the following outcomes using the following instruments:

After the study enrollment and the first primary data collection (t0-1), the assessment with SmED-Patient and SmED-Contact + will take place preferably before the first contact with the treating physician. According to the objectives of the study, both applications are used to measure the agreement between both SmED versions. The assessment with SmED-Contact + is expected to take 2–3 min and will be performed by the study personnel. Assessments are conducted exclusively by study personnel with certified training in the use of SmED-Contact +. The application of SmED-Patient is done by the patients themselves and takes on average 3–4 min. The results of both SmED assessments will be blinded to the patient and the study personnel as well as clinical personnel. The order of the SmED applications will be randomized in order to control the possible mutual influence on the response behavior of the patients.

In a pilot study, the treating ED nurses are tasked with assessing the patient’s treatment urgency and the level of care required, based on the initial medical assessment (triage) (see Fig. 1). An adaption of a validated assessment sheet [13] is employed to assess the treatment urgency (according to Table 1) and the appropriate level of care (according to Table 2). Table 5 outlines the criteria utilized by the nurse as well as their evaluation basis in making this assessment.

**Table 5 Tab5:** Attending nurse assessment of treatment urgency and care level

Assessment sheet	Evaluation basis
• Assessment of mobility	• Vital parameters, triage category, lead symptom, overall clinical impression and anamnesis
• Assessment of general condition	
• Assessment of treatment urgency and appropriate care level	

Furthermore, in a sub-group of *n* = 30–60 patients, ED physicians evaluate the utility of SmED-Patient retrospectively. They therefore receive a summary (short report) of the SmED-Patient assessment as well as all routine ED data as well as the further hospital course in case of admitted patients. The ED physicians provide an evaluation of the digital anamnesis and symptom assessment generated by SmED-Patient in terms of completeness and appropriateness of the questions asked. They also assess the utility of the SmED-Patient summary for assessing patients’ complaints and treatment urgency in routine ED care. For this purpose, a separate assessment sheet has been developed. This assessment is conducted subsequent to the patient’s treatment and is based on a comparison of the symptom summary provided by SmED-Patient and the medical routine data. Table 6 outlines the criteria utilized by the physicians in making this assessment, as well as the variables derived from the routine data set.

**Table 6 Tab6:** Attending physician evaluation of the symptom assessment and the utility of the SmED-Patient summary

Assessment sheet	Evaluation basis
• Evaluation of completeness, appropriateness and utility of SmED-Patient symptom assessment summary	• Vital parameters
	• Triage category
	• Leading symptom and medical anamnesis
	• ED diagnostics, diagnoses, treatment as well as data from inpatient stays and discharge data from the ED and hospital
	• SmED-Patient symptom assessment (summary version)

Legend: *ED* emergency department, *SmED* Structured Initial Medical Evaluation Assessment Germany (German: Strukturierte Medizinische Ersteinschätzung Deutschland), *SmED-Patient* Self-Assessment Version of SmED

Finally, routine data from the ED and hospital documentation system are extracted.

The order of the study measures is as follows: (1) primary data collection part 1 (t0-1), (2) use of the SmED assessments in randomized order: SmED-Patient and SmED-Contact +, preferably prior to the first encounter with the treating physician (t0-2); (3) primary data collection part 2 (t0-3) following the SmED-Patient assessment and potentially after first contact to the treating physician; (4) primary data collection part 3 (t0-4), and (5) assessment by the treating nurse at a variable time during the ED stay; (6) extraction of routine data by the study personnel at the end of the clinical case. The physician’s assessment (7) of the patient sub-sample *n* = 30–60 is conducted retrospectively after the completion of clinical data extraction (see Fig. 2).

Mandatory study measures for a case to be considered valid include the SmED-Patient assessment and regular termination of ED treatment and extracted routine data.

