Sociodemographic and socioeconomic baseline data	Validated instruments from established survey panels (e.g., SOEP & ALLBUS) [26, 27]
Patients’ perspective on utility of SmED-Patient in the ED	Measured using the G-MAUQ-S [28], supplemented by dimensions of comprehensibility, confidence with responses, trust and hypothetical compliance as well as preparedness for the medical consultation
Hypothetical compliance with SmED-Patient advice	Prompted with a patient vignette for influenza and advice to seek outpatient care within 24 h, based on [20]
Physicians’ perspective on utility of SmED-Patient in the ED	Measured using an adapted instrument tested within the research group [13]

Legend: *ALLBUS* German General Social Survey, *SOEP* Socio-Economic Panel Germany, *G-MAUQ* German version of the mHealth App Usability Questionnaire, *HLS19-Q12* Instrument to measure General Health Literacy, *HLS19-COM-P-Q6* Instrument to measure Communicative Health Literacy in interaction with physicians, *ED* emergency department

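### Questionnaire items that the protocol calls sensitive to the physician encounter can, as written, be answered after it, because its statements on part content and timing conflict

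*Protocol article*

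**What the plan says.** Four places in the protocol article bear on what each questionnaire part contains and when it is filled in.

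- **Module 1, description of the parts.** "part 2 (t0-3) includes instruments that are sensitive to the physician encounter (e.g. reasons for ED presentation, see Table 4". Of the last part it says "Part 3 is not considered bias-sensitive" and "It can be collected independently of the time of the physician encounter".
- **Module 1, order of the study measures.** Step 3 is "primary data collection part 2 (t0-3) following the SmED-Patient assessment and potentially after first contact to the treating physician". Part 3 follows as step 4.
- **Participant timeline {13}.** "part 2 at t0-3 includes patients’ utility assessment of SmED-Patient", and "part 3 at t0-4 includes patients’ reasons for ED presentation and questions on health literacy".
- **Recruitment {15}.** The prospective patient survey, like both SmED applications, is done while the patient waits for the first physician encounter.

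Under Secondary outcomes, patient utility covers, among other dimensions, "trust and hypothetical compliance as well as preparedness for the medical consultation". Table 4 lists reasons for ED presentation as a target variable of its own.

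**The concern.** The questionnaire is divided so that contact with the physician cannot colour the answers that it might change. That purpose is lost if the sensitive part may be completed after the contact, or if the sensitive instrument sits in the part that carries no restriction relative to it.

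Two sets of data are exposed. Reasons for ED presentation is the protocol's own example of an item that the encounter can influence. The utility items include preparedness for the consultation. Rated beforehand, preparedness is an expectation; rated afterwards, it is informed by how the consultation went. Either could be a legitimate measure. A mixture of the two with no rule is neither, and a reader of the results could not tell how much of each it contains. The Background and rationale section names better preparation for the symptom conversation as one of the benefits that such tools might bring, so this item is not peripheral to the study's argument.

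**Working it through.** The protocol gives no figure on this point to reproduce. The check is a comparison of the statements.

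**1. Timing of part 2.** Module 1 contrasts part 2 with part 3: part 2 is sensitive to the encounter, and part 3 is not and can therefore be collected at any point relative to it. The contrast has a purpose only if part 2 is meant to come before the encounter. The order of measures in the same module allows part 2 to come after it. Recruitment {15} allows no such exception. These statements cannot all hold.

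**2. Content of the parts.** Module 1 places reasons for ED presentation in part 2. Participant timeline {13} places it in part 3. Both cannot be right.

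**3. What staff could do under each reading.**

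| Reading followed | Reasons for ED presentation | Utility items |
|---|---|---|
| Content from Module 1, timing from the order of measures | part 2, may be after contact | not named in Module 1's description of part 2; may be after contact if they belong there |
| Content from Participant timeline {13}, timing from Module 1 | part 3, unrestricted relative to contact | part 2, may be after contact |
| Recruitment {15} governs the whole survey | before contact | before contact |

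Only the last row protects the sensitive items. Under it, the allowance for a late part 2 and the statement that part 3 is independent of the encounter would have no function. The text does not say which row applies.

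**4. Does another table settle it?** Table 8 lists t0-3 and t0-4 under baseline, ahead of the columns for the nurse and physician encounters. This suggests an intended order but is not a rule: the nurse assessment also has a fixed column there, yet the order of measures puts it at a variable time during the stay. Fig. 1 is not shown. It may give the intended order, but it would not remove the conflict in the text.

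**5. Size.** The shift in an overall mean from late answers is (share answered after contact) × (mean difference between late and early answers). The documents give neither factor, so no value can be put in.

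**6. Reach.** The primary endpoint compares the binary care level from the SmED-Patient assessment (t0-2) with that of the expert panel, which works from routine clinical data. No item from part 2 or part 3 enters it. The target of 150 evaluable patients is derived from that comparison alone.

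**The case against.** The best case for the plan is that collection before contact is clearly the default. Patients with prior physician contact in the ED are excluded, eligible patients are approached before the first encounter, and both Recruitment {15} and the opening of Module 1 place data collection in the waiting period. The allowance in the order of measures then reads as a contingency for patients who are called in early. This is a fair reading of the intention, and the fix below adopts it. It does not remove the conflict, because the text neither limits the allowance to such cases nor says how the resulting answers are treated. It also leaves the placement of reasons for ED presentation unresolved.

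It can also be said that few utility items are likely to be affected. Patients do not see the SmED-Patient recommendation and clinical staff are blinded to it, so the consultation cannot show the patient whether the tool was right. Hypothetical compliance is asked on an influenza vignette. Comprehensibility, usability and response time concern the application itself. This stands, and it narrows the exposure mainly to preparedness. A patient may reasonably judge preparedness after the consultation, but that is an argument for fixing the timing one way or the other.

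Some stronger readings are tempting but not supported:

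- A reader might infer that site or urgency comparisons of utility would be confounded with timing, since the two EDs are organised differently. No such comparison is planned. The utility subgroups are exemplified by health literacy and age, and the comparison between sites is descriptive and concerns demographics.
- A reader might infer that part 3 has no timing at all. It keeps its place as step 4 at t0-4; only its timing relative to the physician is unrestricted.
- A reader might infer that a late questionnaire leads to case exclusion as non-adherence and so reaches the primary analysis. The order of measures expressly permits a late part 2, and the mandatory measures for a valid case do not include the questionnaire.

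**Conclusion.** The point holds as an internal contradiction with a practical consequence. Module 1 declares part 2 sensitive to the physician encounter and then permits it afterwards, against Recruitment {15}. The one instrument named as sensitive is placed by Participant timeline {13} in the part that Module 1 leaves unrestricted relative to that encounter. As written, reasons for ED presentation and the patient-utility items, notably preparedness, can mix answers from before and after the consultation.

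The amount of bias is unknown and may be small: it depends on how many patients are called in early and on how far their answers differ. The conclusion assumes nothing about either quantity. It rests on the wording of the sections and on the protocol's own statement that the encounter is a source of bias. The consequences are confined to secondary and descriptive results.

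**What to change.** - Reconcile Participant timeline {13}, Recruitment {15} and the two statements in Module 1, so that each instrument belongs to one named part with one timing rule.
- Place reasons for ED presentation and the SmED-Patient utility items in the part collected before first physician contact. Allow later collection only as an exception, when the patient is called early.
- Record for each patient whether that part was completed before or after first contact.
- Report these items, including preparedness, overall and separately for the pre-contact answers. Keep the post-contact answers: dropping them would make missingness depend on waiting time.

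The cost is a re-ordering of existing items, one extra flag and one sensitivity analysis, with slightly fewer answers in the pre-contact analysis. If collection has already begun (recruitment was planned from March 2025), the flag and the separate reporting remain possible wherever the relevant times were recorded.

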#### Module 2: expert panel assessment of SmED-Patient recommendation for all cases

An independent expert panel, consisting of primary care physicians (n=2) and physicians working in the ED (n=2), evaluates all valid cases in pairs.The cases will expectedly be divided equally between the pairs, with each case being evaluated independently by two experts. First experts are blinded to the SmED-Patient recommendations and only provided with the initial clinical patient data (routine ED and hospital data). Based on these data the experts provide (1) their own rating of perfect care level and treatment time along the evaluation matrix and (2) their rating of a range of appropriateness of the combination of care levels and treatment times along the evaluation matrix (Table 7). Thereafter the experts are unblinded to SmED-Patient recommendations and evaluate (3) the appropriateness of the SmED-Patient recommendation and (4) potential hazards to patient safety by the SmED-Patient recommendations, both in comparison to the perfect care level and time based on their former rating and the range of appropriate combinations of level of care and treatment time.

**Table 7 Tab7:** Range of appropriateness for SmED-Patient recommendations assessed by an expert panel

